### Secondary outcomes

This study will also evaluate other clinically-relevant outcomes, including: percentage of days positive for buprenorphine administration in between assessments (self-report via Timeline Follow-Back and biochemically verified via Urine Toxicology Screens) and retention in treatment (see Table 2). Retention will be determined by the total number of clinic visits attended, and treatment discontinuation based on electronic medical record review. This study also seeks to identify potential mechanisms that may underlie the efficacy of iCOPE. Therefore, we have selected several other secondary outcomes of interest. These include motivation, distress tolerance, emotional and behavioral self-regulation skills, and negative affect (see Table 2). The readiness ruler assesses current level of motivation to change opioid use [39]. Self-reported DT will be assessed by the Distress tolerance scale [40], which evaluates general tolerance of psychological distress. Behavioral assessments of DT will include the computerized mirror-tracing persistence task [41] to assess psychological DT and a breath-holding task to assess physical DT. The positive affect and negative affect schedule will be used to evaluate negative affect throughout the study [42]. The difficulties with emotion regulation scale [43] will be used to assess the degree to which respondents experience dysregulated emotional states (emotional self-regulation). The UPPS-S impulsive behavior scale will assess a 5-factor model of impulsivity (behavioral self-regulation) [44].

### Feasibility and acceptability

Treatment satisfaction will be assessed by the client satisfaction questionnaire-8 [45] following the computerized intervention delivered at intake and following the text message portion of the study. Usability and acceptability of the text message intervention will be evaluated by the system usability scale [30–32] while satisfaction will be assessed through *the* relative subjective count (rsc). Low RSC correlates with increased patient satisfaction; high RSC reflects poor acceptability of a technology [33] see Table 2.

## Data analysis

### Overview

Considering this is a pilot study, analyses will have the goal of establishing feasibility, acceptability, and estimation of effect sizes, with modest expectations for rejection of null hypotheses. As a first step, the equivalence of treatment conditions regarding key baseline variables will be assessed. This will involve comparisons of treatment conditions on demographics and baseline levels of potential treatment moderators (e.g., gender and age). Should conditions differ on any characteristic, these variables will be placed in models as interactions with group assignment, along with its main effect, and also in a distinct model with the interaction removed. The model with the lowest Akaike Information Criterion (AIC) will be retained. Other preliminary analyses will include patterns of missing data, dropout rates, distributional properties of dependent and other measures, and correlations among outcome measures. Following the intent-to-treat principle, all randomized participants will be included in the analyses. Given the developmental nature of this study, our primary goal is to yield a stable estimate of the effect size rather than to find statistically significant differences. We are aware of the dangers of relying exclusively on small pilot studies to gauge the promise of novel interventions [46]. These effect size estimates have a large standard error, and we primarily will be examining a pattern of results that is supportive of iCOPE, at which point a full-scale trial will be designed to test for a clinically meaningful effect size. Group means on continuous variables typically begin to stabilize around 15 participants per group. For dichotomous or categorical variables, a larger sample size may be needed to provide stable odds ratios for effect size estimates. Our proposed sample size of 60 participants in iCOPE and 20 participants in HE will allow us to evaluate the potential of iCOPE to improve treatment outcomes while maximizing the number of participants in the iCOPE condition to fully assess the feasibility and acceptability of the intervention. A formal power analysis was not completed as this is a pilot trial, which is not designed to detect statistically significant differences between intervention groups [55].

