## Methods

### Study design overview

The current study meets the objectives of Stage I of the NIDA Behavioral Therapies Development Program, which provides a conceptual framework grounded in basic science, for intervention development [26]. Stage I includes two phases—Stage 1A and Stage 1B. Stage 1A involves the creation of a new intervention, while Stage 1B establishes feasibility through pilot testing [26]. In Phase 1 (Stage 1A), our team will develop and refine, through formative evaluation, an interactive computer- and text message-delivered PFI that incorporates DT skills training for persons who have elected to initiate outpatient buprenorphine (iCOPE). Specifically, this intervention is designed to promote medication induction and stabilization following standard clinic intake procedures. All participants will receive standard outpatient buprenorphine treatment, including medication visits, counseling, case management, and peer recovery (treatment as usual; TAU). In Phase 2 (Stage 1B), we will conduct a pilot randomized controlled trial. Eighty patients with a history of OUD, actively seeking outpatient buprenorphine, will be randomly assigned to iCOPE or TAU, using a 3:1 randomization ratio. We propose a 3:1 randomization ratio to maximize the information gained about the iCOPE intervention while including a comparison condition. All participants will complete assessments at treatment initiation as well as 1-, 4-, 8- and 12-weeks post-initiation. These data will be used to inform the development of a large-scale, fully-powered trial. At the time of this report, recruitment for Stage 1A is ongoing.

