### Stage 1B

Stage 1B will employ a randomized controlled trial design to pilot test iCOPE relative to the TAU control condition (see description of treatment conditions below). Adult patients (*N *= 80) meeting eligibility criteria will be randomly assigned to either the iCOPE or TAU conditions.

Following the initial evaluation, in which patients are admitted to buprenorphine treatment, staff will refer potentially eligible patients to study personnel. Interested participants will meet with study personnel in a private setting at the clinic. Informed consent will be obtained, and final eligibility will be determined. Eligible participants will complete a baseline assessment, including two brief behavioral measures of DT (Mirror Tracing and Breath Holding; see Assessments). Participants will then be randomly assigned to iCOPE or TAU. Participants in the iCOPE condition will complete the brief computerized intervention. They will also be informed about the text message element of the intervention and instructed in these procedures. We will recruit 80 participants who will be assigned to condition at a 3:1 ratio, with 60 participants assigned to iCOPE and 20 participants assigned to TAU. Participants will be scheduled to return to the clinic for follow-up appointments consisting of an online survey, behavioral DT measures, and urine collection. Follow-ups will occur at 1-, 4-, 8- and 12-weeks post-treatment initiation.

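### The stated primary goal, a stable effect size, is not something a 60/20 pilot can deliver, so a supportive pattern in those estimates should not be the main trigger for a full trial

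*Protocol article*

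**What the plan says.** All of the following is in the protocol article.

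- Data analysis, Overview, sets the aim: "our primary goal is to yield a stable estimate of the effect size rather than to find statistically significant differences".
- Two sentences later it says: "These effect size estimates have a large standard error, and we primarily will be examining a pattern of results that is supportive of iCOPE". The sentence goes on to say that a full-scale trial would be designed at that point.
- The argument for size is "Group means on continuous variables typically begin to stabilize around 15 participants per group", followed by the concession "For dichotomous or categorical variables, a larger sample size may be needed to provide stable odds ratios for effect size estimates".
- The allocation is justified under Study design overview: "We propose a 3:1 randomization ratio to maximize the information gained about the iCOPE intervention while including a comparison condition".
- Stage 1B gives the numbers, with TAU as the comparator: "We will recruit 80 participants who will be assigned to condition at a 3:1 ratio, with 60 participants assigned to iCOPE and 20 participants assigned". The Overview sentence on size names a different comparator: "Our proposed sample size of 60 participants in iCOPE and 20 participants in HE".
- Primary pilot trial analyses plans a fractional logit model fitted by GEE for abstinence, adherence and retention, on all randomized participants and all available data.
- The Discussion says the results will decide whether to go on to a large trial.

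The article states no precision figure and no attrition rate for the randomized stage.

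**The concern.** The same quantity is described as stable and as having a large standard error, within one paragraph. The 15-per-group mark does not bridge the two. It is about when a single group mean settles, whereas an effect size is a difference of two means and carries the error of both. The paragraph itself allows that odds ratios may need more patients, and the planned model works on the logit scale.

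This matters because of the use made of the estimate. If a supportive pattern is what the team primarily looks for, an imprecise comparison against 20 controls carries most of the weight in the next decision. The part of the trial that 60 iCOPE patients can measure well, feasibility and acceptability, is left without a stated share in it.

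**Working it through.** **Inputs.** From the article: N = 80, 3:1 allocation, four follow-ups (weeks 1, 4, 8, 12), and a mark of about 15 per group. Assumed, because the article gives no figure: unit SD, within-patient correlation 0.3 to 0.7, loss to follow-up, outcome level.

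**The plan's own figure.** 80 × 3/4 = 60 and 80 × 1/4 = 20, so the split reproduces. There is no precision figure to reproduce.

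**One time point, complete data.** SE = √(1/60 + 1/20) = 0.258 SD. With the t quantile on 78 degrees of freedom (1.991), the half-width is 0.514; with 1.96 it is 0.506. So it is about 0.51 SD, and an observed difference of 0.3 SD would have an interval of about −0.21 to 0.81.

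**What 3:1 does to the comparison.** 1/60 + 1/20 = 4/60 = 1/30 + 1/30, so 60/20 compares the arms as precisely as 30/30 would. The TAU arm supplies (1/20)/(4/60) = 75% of the variance.

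**Average of four visits, complete data.** The half-width is multiplied by √((1 + 3ρ)/4).
- ρ = 0.3: 0.514 × 0.689 = 0.35 SD
- ρ = 0.7: 0.514 × 0.880 = 0.45 SD

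**Assumed 25% loss in each arm (45/15), one time point.** SE = √(1/45 + 1/15) = 0.298, and × 2.002 gives 0.60 SD. The control arm is then exactly at the 15-patient mark, so reaching the mark does not make the difference precise.

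**Logit scale.** For a binary outcome at an assumed 50% in both arms, SE(log OR) = √(1/(20 × 0.25) + 1/(60 × 0.25)) = 0.516. The 95% interval is the odds ratio divided and multiplied by exp(1.96 × 0.516) = 2.75. A fraction with the same mean varies no more than this, so this is the outer case at that level and a single time point.

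**A proportion in the iCOPE arm, n = 60.** The half-width is 1.96 × √(p(1 − p)/60): 0.101 at p = 0.8 and 0.127 at p = 0.5, or about ±10 to 13 points.

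**GEE standard errors.** Null fractional logit GEE trials were simulated at 60/20 with assumed beta-distributed outcomes. The uncorrected sandwich z-test rejected in 6.0% to 7.9% of trials at nominal 5%. The Mancl-DeRouen correction with t quantiles rejected in 4.7% to 6.4%, with standard errors 4% to 5% larger. A run of 1,500 trials per setting, with working independence and 0% or 40% dropout, gave 6.4% to 7.2% against 4.9% to 6.0%. Monte Carlo error there is about √(0.05 × 0.95/1500) = 0.6 points.

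**The case against.** The paragraph is candid. It admits the large standard error, warns against relying only on small pilots, says the trial is not designed to detect significant differences, and lists feasibility and acceptability as goals. A careful reader would not be misled about power, and a pilot does not need a power analysis. This stands, and it makes the problem one of a misstated goal and a poorly placed decision rule, not of concealment.

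The 0.51 SD figure is for an unadjusted comparison at one visit, whereas the plan is a repeated-measures model with covariates on the logit scale. This also stands. The averaged range of 0.35 to 0.45 SD is given for that reason, and covariates could narrow it somewhat. Neither figure is the precision of the planned estimate; both are yardsticks.

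Three stronger readings are tempting, and the article does not support them.

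- *The design fails its own mark of 15 after attrition.* Twenty controls exceed 15, and the arm falls below it only if more than 5 of 20 (25%) are lost. No attrition rate is given. The nearly-half figure in the Abstract and Discussion is failure to stabilise on treatment, not loss to the study. Assessments are aligned with clinic visits, GEE uses partly observed patients, and retention is read from visit counts and the medical record.
- *The next trial will be launched on the signs of three estimates.* The wording is a supportive pattern, with no rule that every outcome must point the same way. Chance probabilities for such a rule would test something the article does not say.
- *The plan uses uncorrected robust errors.* The article does not name the variance estimator, which may be fixed in the analysis plan. The correction is an improvement to adopt, not an error found.

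**Conclusion.** The point holds as a contradiction in the stated primary goal, with a consequence for how the pilot is used. The Overview promises a stable effect size that its own next sentences and its design do not provide, and the 15-per-group argument is about a different quantity. The half-width is about 0.51 SD at one time point with complete data, about 0.35 to 0.45 SD averaged over four visits if within-patient correlation lies between 0.3 and 0.7, and wider with any loss (0.60 SD at one time point with an assumed 25%). Intervals this wide cover effects from none to large, so a supportive pattern should not be the primary trigger for a full-scale trial.

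The small-sample issue with GEE is modest, about 6% to 8% rejection at nominal 5% under assumed beta outcomes, and secondary. HE is a clerical slip: it is not in the abbreviation list, Study design overview and Stage 1B say TAU, and the section on TAU argues against a health education control. A reader might infer that a different comparator is planned; nothing else in the article supports that.

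**What to change.** 1. In Data analysis, Overview, replace the promise of a stable effect size with estimation of effects with 95% confidence intervals. State the expected precision and its assumptions: about 0.51 SD at one visit, 0.35 to 0.45 SD averaged over four visits at correlation 0.3 to 0.7, and about 0.60 SD at one visit with 25% loss. Say that these are yardsticks in SD units, not the precision of the fractional logit effect. Drop the 15-per-group sentence or limit it to group means.
2. Rest the decision to proceed mainly on feasibility and acceptability in the iCOPE arm. Report efficacy estimates as intervals and do not judge them by direction.
3. Use small-sample-corrected GEE standard errors (Mancl-DeRouen, or EMPIRICAL=MBN in GLIMMIX) with t quantiles.
4. Change HE to TAU.

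The cost is wording, one software option and a less flattering precision statement. Intervals widen by 4% to 5% from the corrected standard error, and by about 6% to 7% once the t quantile is counted (1.991/1.960 = 1.016; 1.04 × 1.016 = 1.06 and 1.05 × 1.016 = 1.07). Sample size, allocation and visits are unchanged.

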### Primary pilot trial analyses

Tests of the effects of treatment on the primary outcome variables (abstinence, adherence, retention) will be conducted using a fractional logit model [47] estimated by Generalized Estimating Equations (GEE) [48, 49]. GEE is a quasi-likelihood estimation method of repeated measures for modeling of covariance structures when outcomes are correlated across time. It allows for inclusion of both categorical and continuous independent variables. The fractional logit model can be used for any fractional outcome with a range of 0 to 1 and can be readily implemented using SAS PROC GLIMMIX. An advantage of GEE over ANOVA is that GEE models address nesting by adjusting the standard errors of the test statistics based on the covariances (and variances) of nested observations, rather than depending on calculating differences. These variances and covariances can be modeled based on all data available. The primary, between groups, independent variable in the above GEE is treatment group. Variables measured at baseline will be examined using screening runs prior to primary analyses to see which of these baseline variables are most strongly associated with the outcomes. Those that show significant relations with outcome will be entered as additional covariates in the primary analyses unless there are concerns of multicollinearity. The linear effect of time also will be included as a covariate in these analyses. We will test for non-linear (i.e., linear plus quadratic) effects of time for the repeated measures. Analyses will be conducted separately on two overlapping samples. Following the intent-to-treat principle, all randomized participants will be included in the first set of analyses. This is the most conservative approach and represents our main outcome analysis. We also will conduct analyses on subjects who completed the computer-based intervention, the “as-treated” analysis. Although subject to more bias, especially if dropout is a problem, this latter approach answers more directly the question of intervention efficacy by providing an estimate of the maximal effects attained by an intervention. Similar results with both approaches increases confidence in the findings.

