## Abstract

**Background:**

Buprenorphine-naloxone is an evidence-based treatment for Opioid Use Disorder. However, despite its efficacy, nearly half of participants are unsuccessful in achieving stabilization (i.e., period of time following medication induction in which medication dose is adjusted to be effective in reducing cravings/withdrawal, minimize potential side effects, and eliminate illicit substance use). This paper presents the study design and protocol for a digital health intervention designed to promote engagement in and adherence to buprenorphine treatment, offered through an outpatient addiction treatment center, through motivational enhancement and distress tolerance skills training. Personalized feedback interventions represent a promising method to effectively motivate engagement in and adherence to buprenorphine treatment. These interventions are generally brief, individually tailored, and have the potential to be delivered via mobile platforms. Distress tolerance, a transdiagnostic vulnerability factor, has been implicated in the development and maintenance of substance use. Targeting distress tolerance may improve substance use treatment outcomes by promoting the ability to persist in goal-directed activity even when experiencing physical or emotional distress.

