### Compensation and retention

In an effort to bolster study retention, we have aligned study follow-up assessments with routine clinic visits. Additionally, follow-up reminders will occur via emails, telephone calls, and text messages. Participants will earn a $25 gift card for completing the initial assessment and a $20 gift card for completing each follow-up assessment. Participants completing all required follow-ups will earn an additional $25 gift card. Participants have the potential to earn up to $130 for completing all study assessments.

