### Primary outcome

The primary outcome of this study is percentage of days positive for drug use in between assessments (self-report and biochemically verified; see Table 2). The interviewer-delivered Timeline Follow-Back will assess daily opioid use, other illicit substances (e.g., cocaine), and alcohol use. It has demonstrated good reliability [37] and has been validated for the assessment of opioids and other substance use [38]. Urine Toxicology Screens will be administered at all time points to screen for the presence of opioids and other illicit substances.

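### In-clinic outcome visits and available-data GEE leave the drug-use effect at risk of bias of unknown direction, and neither the all-randomised set nor its agreement with the as-treated set guards against it

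*Protocol article*

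**What the plan says.** **Outcome and its collection.** "The primary outcome of this study is percentage of days positive for drug use in between assessments" (Primary outcome), by Timeline Follow-Back and urine screen. Buprenorphine adherence is measured in the same way (Secondary outcomes). Follow-ups fall at 1, 4, 8 and 12 weeks: "Participants will be scheduled to return to the clinic for follow-up appointments consisting of an online survey, behavioral DT measures, and urine collection" (Stage 1B). Table 2 puts the Timeline Follow-Back and urine screens at the same time points. To help retention in the study, "we have aligned study follow-up assessments with routine clinic visits" (Compensation and retention). That section also provides email, telephone and text reminders, a payment for each follow-up and a bonus for completing all of them.

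**Retention.** The Background and Discussion sections relate early lapse to poor retention. The Abstract lists retention among the outcomes iCOPE should improve. Treatment discontinuation is taken from the medical record (Secondary outcomes).

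**Analysis.** "Following the intent-to-treat principle, all randomized participants will be included in the analyses" (Data analysis, Overview). The model is a fractional logit by GEE with arm, time and outcome-related baseline covariates. On its covariance structure the plan says "These variances and covariances can be modeled based on all data available" (Primary pilot trial analyses). The same section describes the all-randomised analysis as the most conservative one, attaches the worry about dropout to the as-treated set (participants who completed the computer session), and treats agreement between the two as added confidence. The Overview plans to describe missing-data patterns and dropout rates.

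**The concern.** Whether drug use is observed is tied to clinic attendance. On the article's own rationale, attendance is related to drug use and may be changed by the intervention. Ordinary unweighted GEE on the available records needs missingness that does not depend on the outcome once the modelled covariates are taken into account. Arm, time and baseline variables are in the model; use after leaving treatment is not.

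Keeping every randomised participant in the analysis set does not restore intervals that were never assessed. The as-treated set loses the same intervals. The computer session is done on site after baseline and randomisation, so most iCOPE participants should complete it and the two sets should nearly coincide. Their agreement would then say little about dropout.

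The article's stated primary goal is a stable effect-size estimate, and the results will inform whether to proceed to a large trial. Differential follow-up could hide or inflate that estimate.

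**Working it through.** **Inputs from the article.** 80 randomised 3:1, "with 60 participants assigned to iCOPE and 20 participants assigned to TAU" (Stage 1B): 80 × 3/4 = 60 and 80 × 1/4 = 20. There is no power figure to reproduce: "A formal power analysis was not completed as this is a pilot trial" (Overview). No dropout or missing-assessment rate is given for this trial. The visit times give outcome intervals of 1, 3, 4 and 4 weeks, so a participant not assessed after week 4 loses 8 of 12 weeks. In TAU each participant is 1/20 = 5% of the arm.

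**Assumed inputs.** Let d be the share who leave treatment, r the share of days with use if retained, l the share after leaving, and q the share of leavers still assessed.

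- Full mean = (1 - d)r + d·l
- Observed mean = [(1 - d)r + d·q·l] / [(1 - d) + d·q]

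**Scenario A: iCOPE acts only through retention** (r = 20%, l = 60% in both arms; d = 35% iCOPE, 50% TAU).

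- Full: iCOPE 0.65 × 0.20 + 0.35 × 0.60 = 0.34; TAU 0.50 × 0.20 + 0.50 × 0.60 = 0.40. Difference -6.0 points, OR 0.77.
- q = 0: 0.20 v 0.20. Difference 0.0, OR 1.00.
- q = 0.5: iCOPE (0.13 + 0.105)/0.825 = 0.285; TAU (0.10 + 0.15)/0.75 = 0.333. Difference -4.8.

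**Scenario C: equal dropout, benefit only in retained patients** (d = 50% in both arms; r = 15% v 20%; l = 60%).

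- Full: 0.375 v 0.400. Difference -2.5, OR 0.90.
- q = 0: 0.15 v 0.20. Difference -5.0, OR 0.71.

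| Scenario | True difference (points) | q = 0 | q = 0.5 | q = 0.8 | q = 1 |
|---|---|---|---|---|---|
| A: dropout 35% v 50% | -6.0 | 0.0 | -4.8 | -5.7 | -6.0 |
| A2: as A, dropout 25% v 50% | -10.0 | 0.0 | -7.6 | -9.4 | -10.0 |
| C: equal dropout | -2.5 | -5.0 | -3.3 | -2.8 | -2.5 |
| D: use unrelated to leaving (20% v 30%) | -10.0 | -10.0 | -10.0 | -10.0 | -10.0 |

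Across these scenarios the bias is at most 2.4 points at q = 0.5 and 0.6 points at q = 0.8.

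**Check with the planned type of model.** A fractional-logit GEE with arm and linear time was simulated over four visits under the scenario A rates. Leaving was spread over the intervals, and leavers kept every interval before they left. At ten times the sample with q = 0, the OR was 0.84 on full data and 1.00 on available data with independence working correlation, and 0.85 and 1.01 with exchangeable. At q = 1 there was no bias. At 60/20 with q = 0, the mean log OR was -0.17 on full data and +0.06 on available data, a bias of about 0.2 against a sampling SD of about 0.25.

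**What weighting can recover.** In scenario A at q = 0.5, giving each assessed leaver weight 1/0.5 = 2 returns iCOPE (0.13 + 0.35 × 0.5 × 2 × 0.60)/1 = 0.34 and TAU (0.10 + 0.50 × 0.5 × 2 × 0.60)/1 = 0.40, hence -6.0. This requires assessed leavers to resemble the unassessed ones. At q = 0 there is nobody to weight.

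**The case against.** Several stronger readings are tempting, and the article does not support them.

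- **That leavers vanish from the analysis.** They keep each interval observed before leaving; only later missed intervals are lost. Only someone with no follow-up at all adds no post-baseline record.
- **That follow-up ends with treatment.** No section says so. Aligning visits is itself a retention measure, and the reminders and payments are not made conditional on staying in treatment. Some leavers may well be assessed.
- **That "nearly half of participants are unsuccessful in achieving stabilization" (Abstract) gives the loss rate.** As defined there, stabilisation includes dose adjustment and eliminating illicit use. It is neither a dropout rate nor a missing-assessment rate.
- **That GEE is valid only if data are missing completely at random.** Missingness may depend on modelled covariates. The doubt concerns dependence on use beyond them.
- **That the estimate is biased, or biased in a known direction.** Scenarios A and C go opposite ways, and D shows no bias.
- **That retention results are equally affected.** Record-based discontinuation does not need study attendance.

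Two further objections carry weight. The sentence on available data concerns covariance modelling in contrast with ANOVA, and detailed missing-data handling may sit in an analysis plan that is not shown. Its absence is therefore not the point here. Also, calling the all-randomised analysis most conservative is a comparison of two analysis sets. What survives is that the article places the dropout problem with the as-treated set and draws reassurance from agreement, although both sets have the same gap.

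**Conclusion.** The point holds as a risk, not as a demonstrated bias. The design ties observation of drug use and adherence to clinic visits, and the article's own reasoning makes missed assessments plausibly related to use and arm. Under the assumed rates the available-data difference can miss a true -6.0 points entirely or double a true -2.5. The error shrinks quickly as more leavers are assessed and is zero if all are. Every rate is an assumption, so size and direction for this trial are unknown.

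The conservatism and agreement statements should not stand as written. Severity is moderate: no confirmatory test is at stake and the article itself expects imprecise estimates, but the worst-case bias is close to one sampling SD and the estimate informs the decision on a full trial.

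**What to change.** 1. **Follow-up.** State that study assessments continue after treatment discontinuation. Where a participant does not attend the clinic, do the Timeline Follow-Back by telephone, and use it to recover missed intervals. This comes first, because no analysis can recover leavers' use if none of them is assessed. The article reports only Stage 1A as recruiting, so this could be settled before the pilot trial.
2. **Analysis.** Pre-specify an inverse-probability-weighted GEE or a multiple-imputation analysis with medical-record retention as a predictor, plus a range of use values for intervals still missing. Report these beside the available-data GEE. With 20 TAU participants, weights or arm-specific imputation models may be unstable, so they are better placed alongside the main analysis than substituted for it.
3. **Wording.** Qualify the most-conservative statement, and say that agreement between the all-randomised and as-treated sets does not address missing follow-up.

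The cost is some time from existing staff for telephone contacts, a little more analysis, slightly wider intervals, and no urine verification for remote contacts.
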